### **statistical analysis technique**

Two independent sample t-test, paired sample t-test

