### **3.3 Study design**

This study is a randomized controlled study. No randomized or any study protocol-driven treatment will be administered or offered to the subjects during the course of the study. If clinically applicable, the treating physician should make the treatment decision and make the choice of treatment options.

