### **.33.3 Research methods and steps**

As this is a randomized controlled study, the physician will decide on the treatment plan according to the instructions and the clinical pathway. The investigator will review the patient's medical history and test report and determine patient eligibility based on the inclusion and exclusion criteria. Patients must sign the latest IRB / IEC approved informed consent (I C F) before performing data collection. In this non-intervention study, the investigators collected clinical assessment data at baseline and after the intervention (2 weeks).

(1) Informed consent and enrollment

Subjects who provided informed consent and met all other inclusion / exclusion criteria were considered as enrolled in the study.

(2) Subject identification number

The numbers were grouped by random number table, and each subject was given a unique identification number (one researcher selected the second column in the third row according to the random number table, all numbers divided by 2, odd to the control group and even to the observation group). This identification number will be used for all study documents (such as a language assessment form, etc.). Furthermore, according to the data privacy regulations, unique identification numbers are allowed as long as it does not contain combined information that identifies the subject.

(3) Research process:

The observation group is receiving routine treatment (including medication, routine care in neurology department, and speech rehabilitation)

Teaching guidance, etc.) on the basis of computer assisted aphasia idiom reading training, the specific method for the use of computer software Powerpoint2003, computer screen in turn white background black idioms (idioms from the student practical idiom dictionary), a total of 50, the computer screen will display idioms, idioms in the form of words, idioms are equipped with auxiliary reading prompt material, including the corresponding idioms unsealed or expanded into the form of characters, words, sentences, paragraphs. At the bottom of the screen, there are the button of each prompt and the button to switch the next idiom. First, the speech rehabilitation teacher asks the patient to read the idiom. When the patient cannot read the idiom, click the corresponding prompt button (voice, video or picture prompt) to help the patient read. The training period is 2 weeks, per day for 40 minutes, the training ground is a clinical classroom.

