### **3.5 Statistical analysis**

#### **3.5.1 Statistical Methods**

Statistical analysis was performed using the statistical software SPSS20.0, Data are represented in terms of ( $\bar{x} \pm s$ ), The study language function score and patient general data (age and disease duration) are the measurement data, Therefore, the t-test of two independent samples was used to compare between the experimental and

control groups, Two respective internal pre-posterior scores were compared using a paired sample t-test, Meverage of language function difference before and after the study using paired sample t-test; patient general data (including sex and stroke type) are count data, The chi-square test was used, Significance level =0.05.

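### Section 3.5.1 assigns a paired t-test to the before-after difference in language function, which leaves the change score without a valid comparison between arms

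*Protocol*

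**What the plan says.** The trial has two parallel arms: "This study is a randomized controlled study" (section 3.3). Patients are allocated by the parity of random numbers, "odd to the control group and even to the observation group" (Research methods and steps). Scores are collected at baseline and at 2 weeks.

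Section 3.5.1 assigns three t-test analyses:

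1. Between arms, for the language function score, age and disease duration: "the t-test of two independent samples was used to compare between the experimental and" control groups. No time point is named for the score, and neither change nor baseline adjustment is mentioned.
2. Within each arm: "Two respective internal pre-posterior scores were compared using a paired sample t-test".
3. For the before-after difference: "Meverage of language function difference before and after the study using paired sample t-test".

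The level is given as "Significance level =0.05", without sidedness. The statistical entry in the protocol summary reads only "Two independent sample t-test, paired sample t-test" and does not say which test answers which question.

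**The concern.** The second analysis already covers pre versus post inside each arm, so the third is either a different comparison or a repetition. Neither reading gives a sound test of whether patients in the training arm improved more than controls.

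The study's purpose is the rehabilitation effect of the idiom training, and improvement over 2 weeks is the natural way to express it. Both arms receive medication, routine neurology care and speech rehabilitation guidance, and both are scored at baseline and at 2 weeks. Any gain from routine care, spontaneous recovery or repeat testing is therefore common to both. A within-arm paired test cannot separate that gain from the effect of training. If the report rests on a significant change in the observation arm, or on one arm being significant and the other not, it does not estimate the treatment effect.

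**Working it through.** The plan states no figure on this point to reproduce. The check is first one of logic and then an illustration under stated assumptions.

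**Reading A: the third clause compares change between arms.** A paired test needs a natural pair for each patient. Parity allocation puts different patients in each arm and defines no matching, so any pairing would be arbitrary and the result would depend on it. Unequal arms cannot be fully paired. If each patient is equally likely to go to either arm, the chance of exactly equal arms is C(N, N/2)/2^N. The protocol gives no N, so the values below are assumed:

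- N = 40: 12.5%
- N = 60: 10.3%
- N = 80: 8.9%

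**Reading B: the third clause repeats the within-arm test.** No test then compares change between arms. Suppose training has no effect and both arms share a mean gain of g, in units of the SD of change. Assumptions: n = 30 per arm, normal change scores, two-sided 0.05. The paired t-test in one arm is significant with probability p, from the noncentral t distribution with 29 degrees of freedom and noncentrality g√30. The arms are independent, so the pattern of observation arm significant and control arm not has probability p(1−p).

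| g | g√30 | p | p(1−p) |
|---|---|---|---|
| 0.2 | 1.10 | 0.184 | 0.150 |
| 0.3 | 1.64 | 0.355 | 0.229 |
| 0.37 | 2.03 | 0.500 | 0.250 |
| 0.5 | 2.74 | 0.754 | 0.186 |
| 0.7 | 3.83 | 0.959 | 0.039 |

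The product p(1−p) cannot exceed 0.25, so 25% is the ceiling. At g = 0.7 the misleading pattern is rare because both arms are usually significant (0.959² = 0.92). A valid two-sided between-arm test would falsely favour training in 2.5% of trials (half of 5%).

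**Simulation check** (20,000 runs per setting; 20, 30 or 40 per arm; shared gain 0 to 0.8 SD; no training effect). At n = 30 the discordant pattern occurred in 15.1%, 23.0% and 18.4% of runs at gains of 0.2, 0.3 and 0.5 SD, which agrees with the table. Across all settings its highest rate was 24.4%. An independent-samples t-test on the change scores rejected in 4.8% to 5.3% of runs at every setting, so the shared gain cancels.

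**Value of baseline adjustment** (assumed: 30 per arm, true effect 0.5 SD of the score, baseline-to-2-week correlation r). The analysis SD is 1 for the 2-week score alone, √(2(1−r)) for change and √(1−r²) for ANCOVA.

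| r | Power, 2-week score alone | Power, change | Power, ANCOVA |
|---|---|---|---|
| 0.5 | 49% | 49% | 61% |
| 0.7 | 49% | 71% | 77% |
| 0.9 | 49% | 99% | 99% |

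**The case against.** The strongest reply is that the plan already contains a between-arm test. Section 3.5.1 applies an independent-samples t-test to the language function score, and the summary lists that test first. Applied to the 2-week score in a randomised trial, it is valid, and shared gains cancel. This stands. A reader might infer from the third clause that the trial has no between-group comparison, or that type I error for the treatment effect is uncontrolled throughout. The protocol does not support either inference. The existing test does not repair the third clause, however: it names neither the change nor the time point.

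Second, the protocol never says that efficacy is declared when one arm is significant and the other is not. That also stands, so the 4% to 25% range is conditional on such a reading and is not the trial's error rate. The gain of 0.37 SD is simply where the product peaks at n = 30. The documents give neither N nor the size of any shared gain. Eligibility requires stable disease, which may limit recovery but does not exclude it.

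Third, the clause may be a translation slip, and a paired test across unequal arms would probably be noticed when it failed to run. This lowers the seriousness, but the clause still needs correcting.

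Fourth, baseline adjustment and confidence intervals are commonly left to a statistical analysis plan, and section 3.4 refers to a statistical plan. Their absence is therefore not an error in this protocol, and adjustment is not needed for validity under randomisation. The protocol does, however, positively assign the wrong kind of test to the before-after difference.

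**Conclusion.** The third clause is wrong as written. Either it applies a paired test to unmatched arms, or it leaves the before-after change with no between-arm test. This conclusion follows from the text and the design and needs no numerical assumption.

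The size is illustrative only: 4% to 25% discordant results under no training effect, with 25% the maximum, against 2.5% for a valid test. It rests on an assumed 30 per arm, a shared gain of 0.2 to 0.7 SD of change, two-sided 0.05, and a reading rule that the protocol does not state.

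The point should be corrected before analysis, but it is not critical, because section 3.5.1 already provides a between-arm t-test of the score. Baseline adjustment is a nearly free gain in precision and not the repair of an error.

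**What to change.** - In section 3.5.1, replace the paired t-test of the before-after difference with a between-arm comparison of the 2-week ABC and CADL scores adjusted for baseline (ANCOVA), reported as a mean difference with 95% CI. The minimum correction is an independent-samples t-test of the change scores.
- State that the treatment effect is judged from this comparison, and that the within-arm paired tests are descriptive only.
- Align the statistical entry in the protocol summary.

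The cost is a few sentences in two places. Both scales are already scheduled at baseline and after the intervention, and the analysis needs no new software.

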### **3.5.2 Statistical software**

SPSS20. 0

### **3.6 Safety evaluation**

The intervention of this study is language function rehabilitation training, without invasive operation and medication. During the intervention and during the intervention, the doctors doctors determine the suitability to conduct and continue to participate in language rehabilitation training. Any discomfort during the course of the intervention. Furthermore, the study interventions were performed in the patient's department without going out.

